**Other**				
	Opiate Treatment Index (OTI-other drugs) [70]^b^	✓	✓	✓
	Assessment of Quality of Life (AQoL) [71]	✓	✓	✓
	McLean Screening Instrument for Borderline Personality Disorder (MSI-BPD) [72]	✓	-	-
Program feedback		-	✓	-

^a^AUDIT-consumption items only

^b^modified to collect only general drug use data

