### Inclusion and Exclusion Criteria

Inclusion criteria include: (1) 18-25 years old, (2) current depressive symptoms (score of ≥7 on Depression Anxiety Stress Scale-21-DASS-21-Depression) [62], (3) harmful drinking as measured by the Alcohol Use Disorders Identification Test (AUDIT) (score of ≥8) [63,64], (4) ability to access the Internet (either in the private residence of the participant, or willingness to use the public library/other suitable venue with Internet access), and (5) Australian residency.

Exclusion criteria include: (1) psychotic symptoms screener score ≥3 [65], (2) non-English speakers, (3) serious risk of suicide (serious past 2-week thoughts of suicide and desire to act), and (4) daily use of cannabis/weekly use of amphetamines.

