### Primary Outcomes

Depressed mood is measured by the PHQ-9 [67], and alcohol use quantity and frequency is measured by the TOT-AL [68]. Prior experience with the target population suggests that both the treatment and attention-control groups are likely to show a decrease in these primary outcomes. We will also calculate reliable change indices (RCI) for depression and alcohol use at each time point relative to baseline to detect reliably significant change in primary outcome measures. RCI’s will be calculated using the methodology outlined in Jacobson and Truax [73], that is-(Ss_post_ – Ss_pre_)/SE_diff_ . Participants with an RCI of 1.96 or greater and who no longer meet the entry criteria for depression or hazardous/harmful alcohol use will be considered to have produced clinically and reliably significant change in these primary outcomes.

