### Secondary Outcomes

In this study, the AQoL measures general functioning and quality of life [71], and depression/anxiety/stress symptomatology is measured by the DASS [62]. Hazardous alcohol use is measured by the AUDIT [63], and AUD criteria are measured by the CIDI-alcohol [69]. Engagement will be measured by a process analysis using website visit data.

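### The alcohol half of the clinically significant change rule cannot be evaluated as written, because the full AUDIT it needs is not collected after baseline

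*Protocol article*

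**What the plan says.** Four statements in the protocol article bear on this point.

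- **Inclusion and Exclusion Criteria.** The alcohol criterion is "harmful drinking as measured by the Alcohol Use Disorders Identification Test (AUDIT) (score of ≥8", that is, a total of 8 or more. No cut-off for the consumption items is given anywhere.
- **Primary Outcomes.** The authors will compute "reliable change indices (RCI) for depression and alcohol use at each time point relative to baseline". The responder definition then covers "Participants with an RCI of 1.96 or greater and who no longer meet the entry criteria for depression or hazardous/harmful alcohol use". Both parts must hold.
- **Secondary Outcomes.** "Hazardous alcohol use is measured by the AUDIT", with no restriction to particular items.
- **Table 1.** The AUDIT is ticked without restriction at baseline. At 5 weeks, and at 12 and 24 weeks, the tick carries footnote a: "AUDIT-consumption items only".

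Table 1 also shows PHQ-9, DASS-21, TOT-AL and the CIDI alcohol section at every assessment, without restriction.

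**The concern.** The responder rule asks at each follow-up whether a threshold on the full AUDIT is still met, but after baseline the full AUDIT total does not exist. An analysis plan cannot recover items that were never asked. Whoever analyses the trial must therefore choose a substitute threshold, possibly with follow-up data in view, for the outcome that will carry the trial's statement about clinically meaningful change in drinking.

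The secondary outcome has a milder form of the same fault. Read literally, it sets a baseline total against a later sub-score, which are different quantities.

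**Working it through.** **The plan's own figure.** The only computed figure in the article is the sample size. With effect size 0.50, 80% power and a two-sided test (alpha 0.05 assumed, as it is not stated), the two-sample t-test needs 63.77, so 64 per group and 128 in total. Allowing for 35% dropout, 128 / 0.65 = 196.9, so 197, against the 200 stated. The figure reproduces and does not depend on the AUDIT.

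**What the collected items can establish.** Write the full score as T = C + R, where C is the consumption sub-score and R the sum of the remaining items. The only assumption here is that item scores are not negative, so R ≥ 0.

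- If C ≥ 8, then T ≥ 8: the entry criterion is still met.
- If C < 8, then T may be below 8 or not, depending on R, which is not collected.

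Combine this with the reliable change index (RCI), taking 1.96 or greater as reliable improvement:

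| RCI for alcohol | Follow-up C | Result under the rule as written |
|---|---|---|
| Below 1.96 | any | Not a responder; the AUDIT is not needed |
| 1.96 or greater | 8 or more | Not a responder; criterion still met |
| 1.96 or greater | below 8 | Undetermined |

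A responder must have T < 8, hence C < 8, and so falls in the last row. The collected items can rule participants out but cannot confirm any alcohol responder.

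**If 8 were applied to the sub-score.** The article does not say this will be done; it is the obvious shortcut. Suppose C is a share s of T. Then C < 8 is the same as T < 8 / s.

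- s = 0.60: 8 / 0.60 = 13.3, so follow-up totals of 8 to 13 would pass as having left the criterion.
- s = 0.40: 8 / 0.40 = 20, so totals of 8 to 19 would pass.

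For example, C = 6 and R = 8 give T = 14, which meets the criterion, while 6 < 8 would be read as having left it. The 40% to 60% range is an assumption; the article does not give the item structure.

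**An illustration of the status step alone.** Assume a full score of 0 to 40 with consumption items contributing 0 to 12, baseline totals with mean 14 to 18 and SD 5 to 6, consumption SD 2.2 and correlation 0.6. Among simulated eligible participants with no change at all, the proportion with C < 8 was:

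| Assumed mean of C | Proportion below 8 |
|---|---|
| 6 | 73% to 74% |
| 7 | 55% to 57% |
| 8 | 37% to 39% |
| 9 | 21% to 23% |

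These are not trial data and not rates of false recovery, because the RCI part of the rule is left out.

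**The case against.** The strongest reply is that the rule has two parts. A reader might infer that unchanged drinkers would be counted as recovered. The article does not support that: a truly unchanged drinker should normally fail the RCI part, whatever the AUDIT shows. This stands, and it confines the problem to participants who already show reliable change.

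Other parts of the reply also stand:

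- The article nowhere says that the sub-score will be compared with 8 or with the baseline total. The size of any misclassification is therefore conditional on a misuse that is not stated and on an assumed item share.
- A reader might infer that the contrast between arms is compressed. Nothing in the article shows this. Both arms answer the same items, and a drop from total to sub-score common to both does not by itself shrink a between-arm difference.
- A reader might extend the fault to depression, because entry is "current depressive symptoms (score of ≥7 on Depression Anxiety Stress Scale-21-DASS-21-Depression" while the primary scale is PHQ-9. Both scales are collected at every assessment, so that half can be evaluated. Using two scales is a design preference.
- The secondary outcome can be analysed like for like, since the baseline AUDIT contains the consumption items.
- The responder rule supplements the primary outcomes, and "alcohol use quantity and frequency is measured by the TOT-AL" at every assessment.

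What does not stand is that an analysis plan could settle the matter as mere detail. The article fixes both the threshold and the items collected, and the two do not fit.

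**Conclusion.** The contradiction is real and limited to alcohol. As written, the status part of the responder rule cannot be evaluated for participants with an RCI of 1.96 or greater and a consumption sub-score below 8, at any of the three follow-ups. That conclusion needs only non-negative item scores.

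How many participants this covers cannot be derived from the article. If 8 were applied to the sub-score, the status step would be too lenient for this group, with an effective threshold on the full scale of about 13 to 20 under the assumed 60% to 40% share. The secondary outcome of hazardous use is mislabelled, because only consumption is measured after baseline.

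The continuous PHQ-9 and TOT-AL comparisons, the depression status criterion and the sample size are not affected.

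**What to change.** 1. Restate the alcohol status criterion on a measure collected identically at all four assessments, either the AUDIT consumption sub-score or TOT-AL. Fix and justify the cut-off before follow-up data are examined.
2. Define the secondary outcome as the AUDIT consumption sub-score, computed from the same items at baseline, 5, 12 and 24 weeks, and label it so.
3. If the full AUDIT threshold is kept instead, collect the full AUDIT at 5, 12 and 24 weeks. Adding it only at 12 and 24 weeks would leave week 5 unevaluable, although the rule applies at each time point.

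**Cost.** The second change is wording only, because the baseline items are already held. The first needs no new data but does need a defensible cut-off; the article gives no TOT-AL norms or distribution from which to derive one. Its price is that the criterion then measures consumption and not the full AUDIT construct. The third adds a few online items, and since the Results section says recruitment is under way, it could leave some follow-ups with the full score and some without.

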### Administration of Assessments

Automatic email prompts to complete Internet-based follow-up assessments will be sent to participants at baseline, 5, 12, and 24 weeks post baseline. In line with best practice standards and our previous trial experience, the following strategies are employed to maximize retention in treatment and assessment: (1) email address required at program commencement, (2) individual email will be sent for each separate module, (3) reminder emails will be sent if participant does not complete assessment in six days, and (4) $10 iTunes voucher reimbursement provided for each scheduled assessments.

### Primary Hypotheses

It is hypothesized that integrated treatment for depression and alcohol problems (the DEAL Project) can achieve greater reductions in: (1) depressive symptoms, and (2) alcohol use, compared to an attention-control condition at 5, 12, and 24 weeks post baseline.

Secondary aims include the examination of: (1) general functioning and quality of life, (2) depression/anxiety/stress symptomatology, (3) hazardous alcohol use, (4) AUD criteria, and (5) engagement across the conditions.

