**Methods:**

The evaluation will take the form of a randomized controlled trial (RCT), comparing the DEAL Project with an attention-control condition (HealthWatch). The RCT will consist of a four-week intervention phase and a 24-week follow-up. It will be entirely Internet-based and open Australia-wide to young people 18 to 25 years old. The primary outcomes will be change in depression symptoms and alcohol use at 5, 12, and 24 weeks post baseline. Secondary outcomes include change in general functioning and quality of life, anxiety/stress symptomatology, and a number of other depression/alcohol related outcomes. Process analysis will also measure engagement across the conditions.

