### Interventions

Access to the treatment website for each of the following conditions will be for a period of 10 weeks from the point of randomization.

The DEAL Project program is a 4-week psychological treatment delivered entirely via the Internet. Participants access the Internet-based sessions from their home computer (or other preferred port for Internet access). Participant-selected pseudonym usernames/emails serve as their login code for the website. Content of the sessions is based on cognitive behavior therapy (CBT) and motivational enhancement theory and was developed from the SHADE resource [59]. Major modifications to the SHADE resource included length, language, reduction of text content, modified design and flow of program, and incorporation of youth vignettes. Participants are asked to complete each session of the DEAL Project intervention in sequence, a week apart, from the point of randomization. The website tracks participants’ progress through each weekly module, with automated email reminders sent to the participant’s nominated email address. However, participants are not “locked out” between sessions so they may complete at a faster rate.

There were 4 sessions of the HealthWatch program that were chosen for this study. This is an attention-control condition program first developed for the Australian National University WellBeing Study [66] in which participants read information about various health concerns and complete accompanying surveys. The purpose of this condition is to control for time spent interacting with an Internet-based program. The specific modules and surveys selected for the four weeks (from the complete 12-week set) were those deemed to be more relevant to younger people and include environmental health, physical and mental activity, nutrition, and relationships. These were redesigned to match the DEAL Project in appearance. Preliminary evidence from the WellBeing research trial suggests that the site is not associated with a reduction in depressive symptoms over time in adults.

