### Data Analysis

As mentioned prior, the DEAL Project is based on the SHADE resource. Data from the SHADE trials indicate the program is associated with a 1.53 effect size change for depression and 0.86 for alcohol between baseline and 12-month follow-up assessments. However, given the SHADE intervention is therapist-guided and longer than that of the DEAL Project, we anticipate smaller effect sizes. Therefore, in line with other brief Internet-based alcohol multi-session modularized interventions with effect sizes of 0.56 [33], a more conservative medium effect size of 0.50 was used. These effects sizes were entered into GPower 3.1 [74] in order to estimate the sample sizes required to detect similar differences between the treatment and control conditions in the current study. Power was set at 80% and conservative 2-tailed tests were assumed even though a directional hypothesis is proposed. Based on this testing, a sample size of 64 per group was needed (total N=128). A conservative dropout rate is 35% of participants at follow-up. As such, we will aim to recruit 200 participants to the study. This will ensure that we will have sufficient power to conduct the analysis.

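### Two outcomes at three time points are all primary with no success rule, while the 80% power is for one two-sided comparison

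*Protocol article*

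**What the plan says.** The Abstract (Methods) states: "The primary outcomes will be change in depression symptoms and alcohol use at 5, 12, and 24 weeks post baseline". The Primary Hypotheses section repeats this for both outcomes, "compared to an attention-control condition at 5, 12, and 24 weeks post baseline". The Primary Outcomes section names the instruments: "Depressed mood is measured by the PHQ-9 [67], and alcohol use quantity and frequency is measured by the TOT-AL [68".

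The Data Analysis section gives one sample-size calculation. On the effect size, "a more conservative medium effect size of 0.50 was used". On the test, "Power was set at 80% and conservative 2-tailed tests were assumed even though a directional hypothesis is proposed". The result is "Based on this testing, a sample size of 64 per group was needed (total N=128"). Allowing for 35% dropout, the target is 200, which the section says secures enough power for the analysis. The significance level is not given. Analysis is by mixed or marginal longitudinal models, and the contrast to be tested is not named.

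Three other places bear on which time and which rule matter:

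- Table 1 labels the 5-week visit the endpoint assessment, and the 12- and 24-week visits follow-up assessments.
- The Interventions section says "Access to the treatment website for each of the following conditions will be for a period of 10 weeks from the point of randomization". Week 5 can therefore come before slower users finish, and week 12 is the first assessment after access closes.
- The Objective is to treat co-occurring depression and problem drinking, and the Discussion expects both outcomes to be better. Neither is written as a success criterion.

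**The concern.** The definition of the primary endpoint and the basis of the sample size are protocol content, and this article states both. They do not match. The hypotheses cover two outcomes at three times; the calculation covers one comparison.

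Two things are at stake, under different rules. If both outcomes are needed, the trial has less than the stated 80% chance of reaching its conclusion even when the assumed effect is true for both. If one favourable result is enough, the chance of a false claim of success exceeds 5%. Without a stated rule, the choice between these can be made after the results are seen. The three times also answer different questions, because some participants may still be using the program at week 5.

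**Working it through.** **Inputs from the article.** Two primary outcomes; three times; d = 0.50; 80% power; two-sided; 64 per group; 35% dropout; target 200.

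**Inputs assumed.** Two-sided alpha 0.05, because it reproduces the stated number. Correlation between outcomes 0 to 0.5 and between visits 0 to 0.8; the article gives neither.

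**1. Reproduce the stated size.** Normal approximation: n = 2(1.960 + 0.842)² / 0.50² = 62.8, so 63 per group. The t-based calculation gives 63.77, so 64 per group, with power 80.1%. A one-sided test would need 50 by the normal approximation and does not match. Dropout: 128 / 0.65 = 196.9, so 197, against the target of 200. The figure is right for one two-sided test at 0.05, with no allowance for a second outcome or time.

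**2. Power under explicit rules** (64 per group, d = 0.50 on each outcome, one time, two-sample t test).

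| Rule | Power |
|---|---|
| One outcome, alpha 0.05 | 80% |
| Both outcomes at 0.05, correlation 0 | 0.801² = 64% |
| Both outcomes at 0.05, correlation 0.2 | 66% (simulated) |
| Both outcomes at 0.05, correlation 0.5 | 69% (simulated) |
| Each outcome at alpha 0.025 | 71% |

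For 80% power per outcome at alpha 0.025, the t-based calculation gives 77.3, so 78 per group, 156 in total and 156 / 0.65 = 240 recruited.

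**3. False-positive rate if any one result counts as success.**

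- One joint test per outcome (two tests): 1 − 0.95² = 9.75% if independent; 9.1% at correlation 0.5.
- Six separate per-visit tests: 1 − 0.95⁶ = 26.5% if independent. With correlated tests, by simulation:

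| Between visits | Between outcomes | Any of six |
|---|---|---|
| 0.5 | 0.3 | 23.0% |
| 0.7 | 0.3 | 20.1% |
| 0.8 | 0.3 | 18.2% |
| 0.8 | 0.5 | 17.3% |

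- Both outcomes required, at one named time or with one test each: at most 5%, so no inflation.

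**4. What baseline adjustment could return.** Adjusting for a baseline score with baseline-outcome correlation r raises the effective d to 0.50 / √(1 − r²). At r = 0.3 this is 0.524: power is 70% for both outcomes (independent) and 76% per outcome at 0.025. At r = 0.5 it is 0.577: 81% and 84%. The article does not give r.

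**The case against.** The strongest reply is that the article never commits to six tests at 5%. It states no alpha, plans longitudinal models that could yield one test per outcome, and sets no rule under which any single result would count. Its wording leans towards requiring both outcomes, and then there is no inflation. Alpha allocation and model contrasts are also commonly left to a statistical analysis plan, which is not shown.

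Much of this stands. A reader might infer that the trial has a false-positive rate of 20% to 26%. The documents do not support that as a property of the trial: it needs separate per-visit tests, an any-of-six rule and visit correlations up to about 0.7, none of which is stated. A reader might also infer that the 80% belongs to only one of the six comparisons. It does not: it is the power of each, if its true effect is 0.50. And the inflation figures and the joint-power figures belong to mutually exclusive rules, so they cannot both be charged to the trial.

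The power figures above are also for a simpler analysis than the one planned. Repeated measures and partial data from the 200 recruited could add information.

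The reply does not remove the mismatch. An unseen analysis plan may hold the testing procedure, but the primary hypotheses and the assurance of sufficient power are made here, and the calculation covers one comparison.

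**Conclusion.** The point holds in this form: two outcomes at three times are all primary, no decisive time or success rule is stated, and the sample size is for a single two-sided comparison. The stated 80% is per-test power, not power for the trial's conclusion. On the article's own effect size and 64 per group, power is about 64% to 69% if both outcomes must succeed and about 71% per outcome at alpha 0.025. If either outcome or any visit could be claimed, the false-positive rate is about 9% to 10% with one joint test per outcome and about 17% to 26% with six separate tests. These results rest on the inferred alpha of 0.05, the assumed correlations and a simple two-sample comparison.

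**What to change.** Before results are known:

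1. Name one primary time point, or one overall longitudinal contrast per outcome, and make the other times secondary. Reconcile the endpoint label for week 5 in Table 1 with the equal status of the three times in the Abstract and Primary Hypotheses. Week 12 is one candidate, as the first assessment after access closes, but the documents do not settle the choice.
2. State one success rule. Either both outcomes must reach two-sided 0.05, which fits the aim of treating co-occurring conditions, or Holm is applied across the two outcomes with a separate claim for each.
3. State alpha in the Data Analysis section and restate the power for that rule.

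The cost is wording and a less favourable power statement. No extra participants are needed if the lower power is accepted; 80% per outcome at alpha 0.025 would need 240 recruited instead of 200. Pre-specified baseline adjustment may recover some of the loss, by an amount that depends on a correlation the article does not give.

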### Primary Outcomes

Depressed mood is measured by the PHQ-9 [67], and alcohol use quantity and frequency is measured by the TOT-AL [68]. Prior experience with the target population suggests that both the treatment and attention-control groups are likely to show a decrease in these primary outcomes. We will also calculate reliable change indices (RCI) for depression and alcohol use at each time point relative to baseline to detect reliably significant change in primary outcome measures. RCI’s will be calculated using the methodology outlined in Jacobson and Truax [73], that is-(Ss_post_ – Ss_pre_)/SE_diff_ . Participants with an RCI of 1.96 or greater and who no longer meet the entry criteria for depression or hazardous/harmful alcohol use will be considered to have produced clinically and reliably significant change in these primary outcomes.

